### Analysis

Continuous variables will be examined with repeated measures analysis of variance and linear mixed models, as appropriate. The proportion of participants who complete the program will be compared between groups using a chi-squared test and the relative risk of non-completion will be determined. All data will be analysed by intention to treat. A per-protocol analysis will also be conducted to reduce the risk of Type 1 error, as recommended in the CONSORT Extension for reporting of non-inferiority and equivalence trials
[48]. Alpha will be set at 0.05.

Sample size calculations are based on the primary outcome of change in 6MWD. If there is truly no difference in the change in 6MWD between home-based and hospital based groups, then 144 participants are required to be 80% sure that the 95% confidence interval will exclude a difference in means of more than 25 metres. We have recently demonstrated that this is the minimal important difference for 6MWD in our population of patients with COPD
[49]. This assumes a standard deviation of the change in 6MWD of 51 metres
[50]. On the basis of our previous trials in pulmonary rehabilitation
[49,50], we expect 15% attrition from the study; we will therefore randomize a total of 166 participants.

This sample size will also provide appropriate power for the secondary outcomes:

***Completion:*** Data from our centres indicate that only 66% people who are referred to pulmonary rehabilitation take up the referral and complete the centre-based program. Previous studies have documented very high completion rates for home-based programs of over 90%
[18]. Using a more conservative estimate of 85% completion, 144 patients will be required to detect a difference in completion rates between hospital and home-based groups (72 in each group).

***Dyspnoea:*** If there is truly no difference in the change in the dyspnoea domain of the CRQ between home-based and hospital based groups, then 142 participants are required to be 80% sure that the 95% confidence interval will exclude a difference in means of more than 2.5 points. This is the minimal important difference for the dyspnoea domain of the CRQ
[51] and assumes a standard deviation of the change in CRQ dyspnoea of 5.1 points
[50].

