**Methods/Design:**

This randomised, controlled, equivalence trial conducted at two centres will recruit 166 individuals with spirometrically confirmed COPD. Participants will be randomly allocated to hospital-based or home-based pulmonary rehabilitation. Hospital programs will follow the traditional outpatient model consisting of twice weekly supervised exercise training and education for eight weeks. Home-based programs will involve one home visit followed by seven weekly telephone calls, using a motivational interviewing approach to enhance exercise participation and facilitate self management. The primary outcome is change in 6-minute walk distance immediately following intervention. Measurements of exercise capacity, physical activity, symptoms and quality of life will be taken at baseline, immediately following the intervention and at 12 months, by a blinded assessor. Completion rates will be compared between programs. Direct healthcare costs and indirect (patient-related) costs will be measured to compare the cost-effectiveness of each program.

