### Recruitment and randomisation

Potential participants will be identified via attendance at respiratory medicine clinics at the Austin or Alfred Hospitals, upon referral to pulmonary rehabilitation at these sites, or screened from the existing database of the pulmonary rehabilitation programs at each site. Eligible participants will be approached by the researchers who will explain the study and provide participants with written and verbal information. The Human Research Ethics Committees of Alfred Health, Austin Health, La Trobe University and Monash University have approved this study, and written, informed consent will be obtained from all participants. Participants will be randomised to the hospital or the home based group using stratified block randomisation, with stratification for site (Austin or Alfred) and disease severity (FEV_1_ < 50% predicted versus FEV_1_ > 50% predicted)
[3]. Randomisation will be undertaken using a computer generated sequence and allocation will be concealed using sealed, opaque envelopes. Participants will be allocated to groups after completion of baseline assessment. The flow of participants through the study will reflect the recommendations of the Consolidated Standard of Reporting Trials (CONSORT)
[26].

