### Outcome measures

Baseline demographics of age, gender, body mass index and lung function (spirometry) will be collected. Spirometry will be repeated at 12 months to determine stability of lung function. Completion rates will be collated at the end of the intervention period and compared between the hospital and home-based groups, with an *a priori* definition of completion as undertaking a minimum of 70% of planned pulmonary rehabilitation sessions
[35].

Clinical measures will be recorded at baseline, immediately following the intervention period (9 weeks) and at 12 months post completion of the intervention. An independent assessor, blinded to group allocation, will undertake the following measurements at each time point following the intervention period.

1) Functional exercise capacity will be measured using the 6-minute walk distance (6MWD), which is a valid measure of exercise capacity in COPD and is responsive to pulmonary rehabilitation
[36]. Two tests will be conducted on each testing occasion using a standardised protocol
[36], with the greatest distance recorded.

2) Dyspnoea will be measured using the Modified Medical Research Council Scale
[37].

3) Disease-specific HRQOL will be measured using the self-reported Chronic Respiratory Disease Questionnaire (CRDQ), a valid and responsive tool in pulmonary rehabilitation
[38]. It is comprised of 20 questions and assesses the domains of dyspnoea, fatigue, emotional function and mastery according to a 7-point Likert scale, with a higher score indicating better HRQOL.

4) A preference-based measure of HRQOL will be derived from the Short-form 36 (SF-36), a generic quality of life measure which is validated in COPD
[39]. Responses to SF-36 will be used to classify health states using the SF-6D, for economic analyses
[40].

5) Self efficacy will be measured using the Pulmonary Rehabilitation Adapted Index of Self-efficacy (PRAISE), a tool derived from the General Self-efficacy scale
[41]. It is composed of 15 statements, each of which is scored from 1 to 4, with a higher score indicating greater levels of self efficacy. It is reproducible and sensitive to change following pulmonary rehabilitation in individuals with COPD
[41].

6) Anxiety and depression will be measured with the Hospital Anxiety and Depression Scale (HADS). This questionnaire is designed to detect and measure the severity of anxiety and depression

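### The primary 6MWD analysis is left open between repeated-measures ANOVA and a mixed model, with no baseline or stratification term mentioned: a modest, avoidable loss of precision

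*Protocol article*

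**What the plan says.** All references are to the protocol article.

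- **Model (Analysis).** One sentence covers every continuous outcome, the primary included: "Continuous variables will be examined with repeated measures analysis of variance and linear mixed models, as appropriate". It gives no rule for choosing between the two methods, no covariates and no separate analysis for the primary outcome.
- **Population and level (Analysis).** "All data will be analysed by intention to treat", with a per-protocol analysis alongside, and "Alpha will be set at 0.05".
- **Primary outcome (Abstract, Methods/Design).** "The primary outcome is change in 6-minute walk distance immediately following intervention".
- **Visits (Outcome measures).** "Clinical measures will be recorded at baseline, immediately following the intervention period (9 weeks) and at 12 months post completion of the intervention".
- **Randomisation (Recruitment and randomisation).** "stratified block randomisation, with stratification for site (Austin or Alfred) and disease severity", the severity split being at an FEV1 of 50% predicted.
- **Equivalence criterion (Analysis, sample size).** The 95% confidence interval for the difference in change in 6MWD is to exclude 25 m. The sizing assumes an SD of change of 51 m, 144 evaluable participants, 15% attrition and 166 randomised.
- **Completion (Analysis).** Compared by a chi-squared test with a relative risk of non-completion; the strata are not used.

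**The concern.** Equivalence here turns on whether an interval fits inside ±25 m, so anything that widens the interval without need lowers the chance of a conclusion. Three features of the text could do that.

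1. Classical repeated-measures ANOVA uses only participants with every visit in the model. Run over baseline, 9 weeks and 12 months, it discards the 9-week result of anyone who misses the 12-month visit, although the primary comparison is at 9 weeks and all data are to be analysed by intention to treat.
2. Baseline 6MWD and the two stratification factors are known for everyone, but the text does not bring them into the analysis. After stratified randomisation, an analysis that ignores prognostic strata overstates the standard error.
3. The usual output of repeated-measures ANOVA is a test of difference. No sentence says which model supplies the 9-week estimate and interval to be set against 25 m.

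**Working it through.** **Inputs from the article:** SD of change 51 m, margin 25 m, true difference 0, 166 randomised, 15% attrition, equal allocation (implied by 72 per group). **Assumed, because the article does not give them:** SD of 6MWD at a visit (80 to 120 m, equal at both visits), variance explained by the strata (5 to 15%), and how the attrition falls between 9 weeks and 12 months.

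**1. The plan's own figure.** For equivalence with true difference 0, n per arm = 2 × [51 × (z + 1.2816)/25]².
- z = 1.645 (90% interval): 71.3, so 72 per arm and 144 in total, as stated.
- z = 1.960 (the 95% interval the text names): 87.5, so 88 per arm and 176 in total.

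The low starting power below is therefore mainly a sizing matter, separate from the choice of model.

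**2. Starting point.** Analysed: 166 × 0.85 = 141. SE = 51 × √(4/141) = 8.59 m, and the 95% half-width is 1.96 × 8.59 = 16.8 m. Power = 2Φ(25/SE − 1.96) − 1 = 0.66. With a 90% interval it would be 0.79.

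**3. Adjusting for baseline.** The correlation is ρ = 1 − 51²/(2S²). The SE ratio of a baseline-adjusted analysis to an unadjusted change score is √[(1 + ρ)/2].

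| Assumed S | ρ | SE ratio | Half-width | Power |
|---|---|---|---|---|
| 80 m | 0.80 | 0.948 | 16.0 m | 0.73 |
| 120 m | 0.91 | 0.977 | 16.4 m | 0.69 |

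The interval is about 2 to 5% narrower, which is under 1 m.

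**4. Adjusting for the strata.** The adjusted SE ratio is √(1 − R²). An unadjusted interval still uses the full SE, while the estimate varies only by SE × √(1 − R²). Its coverage is therefore 2Φ(1.96/√(1 − R²)) − 1.

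| Assumed R² | Interval narrower by | Unadjusted coverage | Power unadjusted | Power adjusted |
|---|---|---|---|---|
| 5% | 2.5% | 95.6% | 0.67 | 0.70 |
| 15% | 7.8% | 96.6% | 0.70 | 0.77 |

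The gains in steps 3 and 4 need not add, since baseline 6MWD and the strata may explain overlapping variance.

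**5. Listwise deletion.** Suppose the 15% is total loss by 12 months. The ratio of complete-case to available-case width is √(n at 9 weeks / 141.1).

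| Assumed loss by 9 weeks | n at 9 weeks | Complete-case interval wider by |
|---|---|---|
| 0% | 166 | 8.5% |
| 5% | 157.7 | 5.7% |
| 10% | 149.4 | 2.9% |
| 15% | 141.1 | 0% |

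**6. The models side by side.** A simulation of 166 participants assumed ρ = 0.8, 8% lost by 9 weeks and 15% in total. Mean 95% half-widths:
- change score, complete cases over three visits: 16.8 m
- change score, all 9-week data: 16.1 m
- mixed model with free baseline means: 16.1 m
- analysis of covariance: 15.4 m
- mixed model with baseline means constrained equal: 15.4 m

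Listwise deletion costs about 4% in width and lack of baseline adjustment about 5%, together about 9%.

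**7. A harsher scenario, assumption only.** If a further 5 to 20 percentage points were lost between 9 weeks and 12 months on top of the 15%, a three-visit ANOVA would analyse 166 × 0.80 = 133 down to 166 × 0.65 = 108. Power would be 0.61 down to 0.44. Nothing in the article predicts this extra loss.

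The effect of stratifying the completion analysis was not quantified; the article gives no completion rates by stratum.

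**The case against.** A condensed article often leaves model terms to the full protocol or analysis plan, so silence on covariates for 6MWD is not a stated exclusion. The same sentence names linear mixed models, which keep participants with partial data. Read with the intention-to-treat commitment, it already permits the better analysis. A repeated-measures ANOVA restricted to baseline and 9 weeks would also keep everyone with a 9-week result. The criterion and time point are stated elsewhere, and either method can deliver the interval. All of this stands, and it limits the point to an open choice that includes a poor option.

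A reader might infer more in four ways that the document does not support.

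- **That the primary model is unadjusted and drops incomplete participants.** No model is fixed. Participants are lost only if a three-visit classical ANOVA is chosen. A mixed model with constrained baseline means already recovers the baseline gain.
- **That unequal loss of outcome data is planned for.** The sizing for completion uses 66% and 85%, hence 34% and 15% non-completion. Completion is defined as undertaking at least 70% of planned sessions, and the 66% also counts referred people who never took up the programme. A non-completer can still be walked at 9 weeks. The only loss figure given is 15% overall.
- **That the low power comes from the model.** The 0.66 arises mainly because 144 matches a 90% interval.
- **That equivalence could be falsely declared.** Ignoring baseline leaves coverage nominal, and ignoring strata puts it slightly above nominal. Listwise deletion could bias the estimate if missing the 12-month visit is related to outcome, but the article gives no basis for a size or direction.

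What the objection does not remove: repeated-measures ANOVA and the unstratified chi-squared test are positively named, and nothing in the text says when the first is to be used.

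**Conclusion.** The point holds as a matter of precision and commitment. The article names a method that, over three visits, would discard valid 9-week results. It does not tie the primary comparison to one model, and it analyses completion without the factors used to stratify randomisation. The consequence is a somewhat wider interval and lower power.

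On the assumed ranges, the separate effects are about 2 to 5% of interval width for baseline, 3 to 8% for strata, and 0 to 8% for listwise deletion if the 15% attrition already covers 12 months. The baseline SD, strata R² and timing of loss are all assumptions, so these sizes are indicative. They are worth recovering because power for the stated 95% interval is only about 0.66 at 141 analysed, and because leaving the method open allows it to be settled after the data are seen.

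**What to change.** Delete the repeated-measures ANOVA option and name one primary analysis: a linear mixed model on all available follow-up 6MWD from randomised participants, with baseline 6MWD, site, FEV1 stratum, visit, treatment and treatment-by-visit. State that the 9-week treatment difference and its confidence interval from this model are compared with ±25 m. Use the same form for the other continuous outcomes.

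For completion, replace the chi-squared test with a Mantel-Haenszel test and a risk ratio of non-completion, both stratified by site and severity.

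The cost is analysis wording only. Every covariate is already collected, and the Trial status section reports that recruitment is continuing. If a full protocol or analysis plan already specifies this model, the article's sentence need only be brought into line with it.

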## Methods

### Design

A randomised, controlled, equivalence trial at two tertiary hospitals (Austin Health and Alfred Health) in Melbourne, Australia.

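### The sample size of 144 gives about 67% power, not 80%, under the stated 95% confidence interval rule; 144 is the number for a 90% interval

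*Protocol article*

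**What the plan says.** The Design section describes "A randomised, controlled, equivalence trial at two tertiary hospitals". The Analysis section then gives every input to the sample size:

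- Outcome: "Sample size calculations are based on the primary outcome of change in 6MWD".
- Assumed truth: "If there is truly no difference in the change in 6MWD between home-based and hospital based groups".
- Criterion, power and number: "144 participants are required to be 80% sure that the 95% confidence interval will exclude a difference in means of more than 25 metres".
- Variability: "This assumes a standard deviation of the change in 6MWD of 51 metres".
- Significance level: "Alpha will be set at 0.05", with no statement of whether this is one-sided or two-sided.

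Equal allocation is taken from the completion calculation in the same section, which splits 144 as "72 in each group". The dyspnoea paragraph repeats the construction with a standard deviation of 5.1 points: "142 participants are required to be 80% sure that the 95% confidence interval will exclude a difference in means of more than 2.5 points". No 90% interval and no pair of one-sided tests at 5% appears anywhere in the article.

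**The concern.** In an equivalence trial the interval must exclude the margin on both sides. A 95% interval lying within the margins corresponds to two one-sided tests at 2.5% each; a 90% interval corresponds to two at 5% each. The two rules need clearly different sample sizes, and the stated number belongs to the second while the text describes the first.

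This affects the primary outcome and the only interval level that the article prints. If the 95% interval is the criterion, the trial has much less chance of showing equivalence than it claims. If the analysis uses a 90% interval to recover the planned power, it departs from the published criterion. A result that passes at 90% and fails at 95% would be open to dispute, or to a choice made after the data are known.

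**Working it through.** **Inputs** (Analysis section): true difference 0; SD = 51 m; margin M = 25 m, read as ±25 m because the design is equivalence; power 80%, so β = 0.20; 1:1 allocation.

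**Formulas** (two one-sided tests, each at level a, true difference 0):

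- n per group = 2 × SD² × (z[1−a] + z[1−β/2])² / M²
- SE = SD × √(2/n)
- power = 2 × Φ(M/SE − z[1−a]) − 1

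**Reproducing the stated 144.** With a 90% interval, a = 0.05:

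2 × 2601 × (1.645 + 1.2816)² / 625 = 71.3, so 72 per group, 144 in total. This matches exactly.

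**The rule as written.** With a 95% interval, a = 0.025:

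2 × 2601 × (1.960 + 1.2816)² / 625 = 87.5, so 88 per group, 176 in total. The exact t calculation gives 89 per group, 178 in total.

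**Power at 144 evaluable.** SE = 51 × √(2/72) = 8.5 m and M/SE = 25/8.5 = 2.941.

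- 95% interval: 2 × Φ(2.941 − 1.960) − 1 = 67.4% (exact t: 66.4%)
- 90% interval: 2 × Φ(2.941 − 1.645) − 1 = 80.5% (exact t: 80.0%)

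**Power at other numbers** (normal approximation):

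| Evaluable | 95% interval | 90% interval |
|---|---|---|
| 144 | 67.4% | 80.5% |
| 141 (166 × 0.85) | 65.8% | 79.4% |
| 166 (no attrition) | 76.9% | 87.0% |

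Even with no attrition at all, the 95% rule falls short of 80%.

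**Can another 95% reading give 144?**

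- One direction only (non-inferiority at one-sided 2.5%): 65.3, so 66 per group, 132 in total. On this reading 144 would give 84% power, not 80%.
- A different SD: 80% power at 72 per group needs SD = 25 / (3.2416 × √(2/72)) = 46.3 m, against the stated 51 m.
- A different margin: it needs M = 3.2416 × 8.5 = 27.6 m, against the stated 25 m.

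None of these agrees with the stated inputs.

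**Dyspnoea.** The ratio of SD to margin is 5.1/2.5 = 2.04, the same as 51/25. The required numbers are therefore the same: 71.3 per group with a 90% interval and 87.5 with a 95% interval. At 142 (71 per group), power is 79.8% with the 90% interval and 66.3% with the 95% interval. The difference between 142 and 144 is only rounding of 71.3.

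**The case against.** The strongest reply is that this is a labelling slip. Two one-sided tests at 5% reproduce 144 and are compatible with an alpha of 0.05 whose sidedness is not given. If that was the intended test, the trial is sized as claimed, only the interval level is misnamed, and the loss of power never arises. This is plausible, and it limits the consequence. It does not remove the contradiction: 95% is the only level printed, it is printed twice, and the document does not settle which was meant.

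Three narrower points also deserve weight.

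- The 95% interval appears only in the sample-size sentences. The analysis paragraph prints no equivalence criterion, and a fuller document may contain one. That is fair, but the sample-size statement is wrong as it stands whatever another document says.
- The two-sided reading is inferred from the equivalence design rather than spelled out. The inference is sound, and the one-directional reading does not yield 144 either.
- The planned repeated-measures or mixed-model analysis might be more precise than an SD of 51 m implies. No baseline correlation is given, so the gain cannot be quantified, and the published calculation itself uses 51 m.

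**Conclusion.** The concern holds. The stated interval level, power and sample size cannot all be true. With a 95% interval required to lie within ±25 m, 144 evaluable participants give about 67% power (66% by exact t) and 80% power needs 176 to 178. With a 90% interval, 144 is correct. The dyspnoea calculation carries the same mismatch, with about 66% power at 142.

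These figures assume a true difference of zero, an SD of 51 m (5.1 points for dyspnoea), equal allocation and an unadjusted comparison of change scores, as the stated calculation implies. The claim that about one trial in three would miss true equivalence applies if the 95% interval is in fact the criterion used. The point must be resolved because it concerns the decision rule for the primary outcome.

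**What to change.** Name one interval level as the equivalence criterion, and use it in the 6-minute walk distance calculation, the dyspnoea calculation and the analysis paragraph. Either choice works with the planned enrolment:

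1. **Keep the 95% interval** and restate power as about 67% with 144 evaluable (66% with 141) for walk distance, and about 66% with 142 for dyspnoea.
2. **Change to the 90% interval**, described as two one-sided tests at 5% each. Make the change before any outcome data are seen and record that this was so. Power is then about 80% at 144 and 79% at 141.

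In either case, state the sidedness of alpha for the equivalence tests.

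The cost is a few sentences and no extra patients. The first choice makes the stated power less favourable; the second accepts a less strict criterion than the one published. Keeping both the 95% interval and 80% power would instead need 176 evaluable, or 176/0.85 = 207.1, so 208 randomised with equal groups, against the planned 166.

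### With 15% attrition, 166 randomised leaves 141 evaluable, not the 144 the plan requires; 144/0.85 gives 170

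*Protocol article*

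**What the plan says.** The sample size paragraph in the Analysis section of the protocol article sets the evaluable target for the primary outcome: "then 144 participants are required to be 80% sure that the 95% confidence interval will exclude a difference in means of more than 25 metres". The inputs are a true difference of zero and a standard deviation of change of 51 metres ("This assumes a standard deviation of the change in 6MWD of 51 metres").

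The allowance for loss follows: "we expect 15% attrition from the study; we will therefore randomize a total of 166 participants". The Abstract (Methods/Design) repeats the total, saying that the trial "will recruit 166 individuals with spirometrically confirmed COPD".

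The article gives no other allowance, rounding rule or attrition rate by time point. The same section then says that this sample size also serves the secondary outcomes, and gives a requirement of 142 for the dyspnoea domain of the CRQ.

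**The concern.** Required number, attrition and randomised number are all printed, and the text presents the third as following from the other two. A loss expressed as a share of participants in the study is a share of those randomised. The randomised number must therefore be the target divided by the proportion retained. Adding 15% of the target to the target gives too few.

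If that happened here, the trial will not reach its own evaluable target under its own attrition assumption. In an equivalence trial the whole confidence interval must lie inside the margin, so lost precision directly reduces the chance of concluding equivalence. The target of 144 has no slack to absorb the loss, because it is already a rounded-up minimum.

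**Working it through.** **Inputs** (protocol article, Analysis, unless noted)

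- Evaluable target: 144 in total
- Attrition: 15%
- Randomised: 166 in total (also in the Abstract)
- Equivalence margin: ±25 m
- Standard deviation of change: 51 m
- True difference: 0
- Allocation: 1:1. This is an assumption for the walk distance; the article gives 72 per group only for the completion outcome.

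**1. Reproducing 166**

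- Target × (1 + attrition): 144 × 1.15 = 165.6, rounded up to 166. This is the printed figure.
- Target / (1 − attrition): 144 / 0.85 = 169.4, rounded up to 170. This is not the printed figure.

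**2. What 166 delivers**

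- Expected loss: 166 × 0.15 = 24.9
- Expected remaining: 166 × 0.85 = 141.1, so about 141
- Shortfall: 144 − 141 = 3
- Highest attrition that still leaves 144: (166 − 144)/166 = 22/166 = 13.3%

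**3. What would keep 144**

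- 170 × 0.85 = 144.5, which meets the target.
- 169 × 0.85 = 143.65, which does not.

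**4. Where 144 comes from**

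For two one-sided tests with a true difference of zero and 80% power (normal approximation):

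n per arm = 2 × [SD × (z(1−a) + z(0.90)) / margin]²

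- a = 0.05 per side (90% interval): 2 × [51 × (1.645 + 1.282)/25]² = 71.3, so 72 per arm and 144 in total
- a = 0.025 per side (95% interval): 2 × [51 × (1.960 + 1.282)/25]² = 87.5, so 88 per arm and 176 in total

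The printed 144 therefore corresponds to a 90% interval, although the text names a 95% interval. Power is shown below on both bases.

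**5. Power at 144 and at 141**

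Power = 2 × Φ(margin/SE − z(1−a)) − 1, with SE = SD × √(2/n per arm)

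- 144 evaluable: SE = 51 × √(2/72) = 8.50 and 25/8.50 = 2.94
- 141 evaluable: SE = 51 × √(2/70.5) = 8.59 and 25/8.59 = 2.91

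| Evaluable | 90% interval (reproduces 144) | 95% interval (as written) |
|---|---|---|
| 144 | 80.5% | 67.4% |
| 141 | 79.4% | 65.8% |

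**6. Secondary outcome**

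The article's requirement for CRQ dyspnoea is 142. The 141 remaining after 15% attrition misses that as well, by one.

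**The case against.** The strongest reply is that the error hardly matters. The gap is four randomised participants (4/170 = 2.4%), power moves by about one percentage point, and the 15% is itself an estimate from earlier trials. This is right about the size. It does not make the printed figures agree.

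A second reply is that the 15% may describe loss over the whole study, which runs to 12 months after the intervention, whereas the primary outcome is measured at about 9 weeks. Loss by then could be 13.3% or less, which would keep 144. That is possible, but the article gives no attrition by time point and applies the 15% directly to the primary-outcome number. As written, the shortfall follows. If the plan relies on lower early loss, it should say so.

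Third, the article does not show the multiplication by 1.15. That is correct: the cause is inferred from an exact match. The finding does not depend on it, because 166 × 0.85 = 141.1 however 166 was reached.

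Fourth, moving to 170 would not repair the sample size, because 144 does not give 80% power with the stated 95% interval. This stands and limits what 170 can be said to achieve.

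**Conclusion.** The concern holds. Under the plan's own 15% attrition, 166 randomised leaves about 141 evaluable, three below the stated 144; 170 would be needed, and 166 tolerates only 13.3% loss. The cost is 1.1 percentage points of power on the 90% interval, which puts it just below the stated 80%, or 1.6 points on the 95% interval. This does not threaten the trial by itself, but a published sample size figure is wrong and should be corrected.

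The counts assume only that the 15% applies to those randomised and to the primary outcome, as the Analysis section presents it. The power figures further assume 1:1 allocation, the stated standard deviation and margin, a true difference of zero and the normal approximation.

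**What to change.** Keep 166 and correct the sentence in the Analysis section. Either of these would do:

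- State that 166 will be randomised and that 15% attrition leaves 141 evaluable. Quote power at 141 and name the interval: 79.4% for a 90% interval, or 65.8% for the 95% interval now in the text.
- State that 166 keeps 144 evaluable if attrition does not exceed 13%. If lower loss is expected by the 9-week assessment, give that rate as the reason.

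This costs one sentence and makes the stated figure slightly less favourable. Design, endpoint and analysis do not change.

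The Trial status section says that recruitment is continuing, so randomising 170 (four more) is an option, with the Abstract changed to match. That restores only the count of 144. The mismatch between the 95% interval and the 144 should be settled at the same time, because it changes the target to which the attrition step is applied. With a 95% interval and 80% power the evaluable target is 176, and 176/0.85 = 207.1, so 208 randomised; multiplying by 1.15 would give only 203.
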